### Randomization

Subjects will be divided into three groups by means of balanced randomization performed with free software (https://www.randomizer.org/). The randomization sequence will only be performed by the principal investigator and auditor.

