## Methods/design

### Sample selection

Individuals with NCNP will be recruited through a text message broadcast on social networks in the city of Seville (Spain) and will be selected based on the eligibility criteria listed below. The study will take place in the facilities of the physiotherapy department of the University of Seville.

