### Exclusion criteria

The exclusion criteria are:Irradiated neck painNeck pain associated with vertigoOsteoporosisPsychological disordersVertebral fracturesTumorsMetabolic diseasesPrevious neck surgeryRed flags (Night pain, severe muscle spasm, loss of involuntary weight, symptom mismatch)Physiotherapeutic treatment continued in the last 3 months

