### Interventions

The participants can only receive the assigned treatment; they cannot combine the treatment with drugs or other physiotherapeutic treatment. Any interference in the treatment will be grounds for exclusion.

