### Sample size calculation

The sample size was calculated using the Granmo calculator v.7.12. Based on the analysis of the variance of means, and estimating an alpha risk of 5% (0.05), a beta risk of 10% (0.10), a unilateral contrast, a typical deviation of 10% (0.10), a minimum difference to detect of 9.8% (0.098) which is based as the minimum clinically important differences in OBI [42], and a rate of follow-up losses of 15%, 10 subjects are required in each group, assuming that there are three groups. Finally, we will include 66 patients who will be divided into three groups, each group with at least 20 subjects, so as to overcome this value to assume the possible loss of follow-up.

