### Blinding

The evaluator and participants in the study will be blinded during the entire process.

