### Trial status

This is the first and definitive protocol versión. Participants will be recruited between January and March 2019. Study completion is expected to be July 2019.

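### The principal investigator, who is not among the blinded roles, helps produce the randomization sequence, and the article does not separate that task from decisions on eligibility or on exclusion after allocation

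*Protocol article*

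**What the plan says.** All places are in the protocol article.

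- **Randomization**, method: "Subjects will be divided into three groups by means of balanced randomization performed with free software". The tool is a public web randomizer. On who does it: "The randomization sequence will only be performed by the principal investigator and auditor". No other role is given this task.
- **Blinding**, on who is kept unaware of the arm: "The evaluator and participants in the study will be blinded during the entire process". The principal investigator is not named here.
- **Sample selection**: individuals "will be selected based on the eligibility criteria listed below". The section does not say who selects them.
- **Exclusion criteria**: the list includes psychological disorders and, among the red flags, severe muscle spasm and "symptom mismatch".
- **Interventions**: "Any interference in the treatment will be grounds for exclusion". The section does not say who decides this.
- **Sample size calculation**: "we will include 66 patients who will be divided into three groups, each group with at least 20 subjects".
- **Trial status**: "Participants will be recruited between January and March 2019".

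**The concern.** A person who makes a list can read it. The article gives this task to the trial lead, jointly with the auditor, and does not count the trial lead among the blinded. Two kinds of decision in this trial leave room for that knowledge to matter.

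The first is entry. Age, current pain and duration of pain leave little discretion, but several exclusion criteria need judgement. Someone who knew the next arm could accept, decline or delay a borderline candidate accordingly.

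The second is exclusion after allocation. Deciding whether a patient has interfered with the assigned treatment is also a judgement. If the person deciding knows the arm, that can affect who stays in the comparison.

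A blinded evaluator protects the measurement of the Overall Balance Index (OBI), pain and disability. It does not protect the make-up of the groups being measured, and bias in that make-up cannot be reliably removed afterwards.

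**Working it through.** The plan gives no figure on this point, so there is none to reproduce. The check is a reading of the sections together, followed by an illustration of size.

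**Reading the sections together**

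1. Who can know the sequence? The Randomization section limits the task to two roles, and one of them is the principal investigator.
2. Is that role blinded? The Blinding section names two parties, and the principal investigator is neither.
3. Does the article keep that role away from selection? Sample selection and Exclusion criteria name no role, so the principal investigator is neither placed in screening nor kept out of it.
4. Does the list exist while patients are being selected? No timing is given. The wording of the method fits a list made in advance. It also fits dividing the whole sample once it is assembled. The calendar does not decide it: recruitment runs from January to March 2019, the last evaluation is at week 12, and completion is expected in July 2019. A single allocation at the end of March would still fit.
5. Does allocating everyone at the end close the problem? For entry, yes, because no upcoming allocation would exist during screening. For exclusion because of interference, no, because that comes after allocation on either reading.

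**Illustration of size**

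Inputs from Sample size calculation: SD 0.10, difference to be detected 0.098, and 66 patients in three groups. Equal groups give 66/3 = 22 per arm.

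Assumptions that are not in the document: k entries in one arm are steered, and each has an OBI result 1 SD better than the patient who would otherwise have taken the place.

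Shift of the arm mean = (k/22) × 0.10. Share of the target difference = shift/0.098.

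| Steered entries | Shift | Share of 0.098 |
|---|---|---|
| 1 in one arm | 1/22 × 0.10 = 0.0045 | 4.6% |
| 3 in one arm | 3/22 × 0.10 = 0.0136 | 14% |
| 3 in each of two arms, in opposite directions | 2 × 0.0136 = 0.0273 | 28% |

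The last row needs six steered entries in total, so it does not belong to the range for one to three.

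**What holding the list adds**

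A simulation of 20,000 runs assumed a single balanced 22/22/22 list. Someone who has no access to the list but always guesses the arm with most places left is right about 42% of the time, against 33% by chance. Someone who holds the list is right every time.

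**The case against.** The strongest objection is that the article states only that the principal investigator helps to produce the sequence. Producing a list and enrolling patients are different tasks, and no section gives the principal investigator any part in screening, treatment or exclusion. The word limiting the task to two roles can itself be read as a safeguard. Custody, concealment and release of allocations are details that an article may leave to the full protocol or to the SPIRIT checklist in Additional file 1, neither of which is shown.

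Much of this stands. A reader might infer that upcoming allocations are in fact known to the trial lead while patients are being selected. The document does not support that. It does not say that the list exists before selection ends, that patients are entered and allocated one by one, or that the principal investigator screens. The lack of a described envelope or release procedure is not a fault of the article either. The illustration is not evidence of bias in this trial: both the number of steered entries and their advantage of 1 SD are assumed, and nothing shows that the judgement-based criteria would select on OBI to that degree.

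The objection does not remove the stated assignment of roles. The article positively places an unblinded trial lead among those who make the list. Limiting the task to two roles does not help if one of the two also decides who enters or who is excluded, and naming the auditor as well does not take away the principal investigator's access.

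It can also be objected that the auditor's independence is not described, and that an auditor who holds the list might later audit their own work. That is fair, and the fix allows for it.

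**Conclusion.** The point holds as a conditional risk that comes from a stated choice of roles. It is not a demonstrated failure of concealment.

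- **Entry:** selection bias is possible if the list is made before recruitment ends and the principal investigator takes part in selection. Both conditions are open in the article.
- **After allocation:** if the principal investigator rules on exclusions for interference, knowledge of the arm can affect who is counted. This does not depend on when the list is made.
- **Size:** under the assumptions above, 5% to 14% of the target difference for one to three steered entries in one arm. The 28% figure applies only to the more extreme two-arm case.

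The change is worth making because it is cheap and because selection bias cannot be repaired once patients are enrolled. Confidence is medium, since the actual roles may be separated in a document that is not shown.

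**What to change.** Change the Randomization section so that the auditor alone generates and holds the sequence. The principal investigator should have no access to it, nor should anyone who screens, treats, evaluates or decides on exclusions. The one exception is that the treating physiotherapist learns each patient's arm when it is released. State that each allocation is released only after that patient's eligibility, consent and pre-evaluation are recorded, for example in sequentially numbered, opaque, sealed envelopes.

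If the auditor is not independent of enrolment, another existing role with no part in enrolment should hold the list instead.

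The cost is the preparation and release of 66 allocations by the role that holds the list. No further patients or measurements are needed.

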### Blinding

The evaluator and participants in the study will be blinded during the entire process.

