### Trial design

This study is a randomized, controlled, parallel, double-blind, three-arm clinical trial of treatment.

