#### Group 1: manual therapy

The “manual therapy” protocol will consist of three techniques based on scientific evidence for the treatment of neck pain [31–33]. These techniques represent a very close approximation to the treatment that is performed in the daily clinic, outside the research protocols.

This protocol will be applied in the three treatment sessions, one per week.High thoracic manipulation on T4 [31]Cervical articular mobilization (2 Hz, 2 min × 3 series) [32]Suboccipital muscle inhibition (3 min) [34].

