#### Group 2: therapeutic exercise

The “therapeutic exercise” protocol will be taught to patients in the first session and should be done once a day during the 3 weeks of treatment. It will be reinforced by the physiotherapist in each of the three individual sessions.

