#### Group 3: sham treatment

For the “control” protocol, the patient will be placed in the supine position, while the physiotherapist will lay his hands without therapeutic intention on the patient’s neck for 3 min, the physiotherapist will simulate the technique of suboccipital inhibition [34]. Later, with the laser pointer off, the patient will be contacted without exerting pressure for 10 s. Patients assigned to the control group will receive treatment 1 or 2 after completing the study.

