## Discussion

This article presents a detailed description of a randomized controlled trial designed to analyze the results in terms of pain, disability, and postural stability of two types of treatments for non-specific chronic neck pain.

We intend to investigate a little-studied field such as postural stability in these subjects and to try to understand the mechanisms that may produce these alterations. We propose two types of treatments: one using manual therapy based on the structural influences of the neck, and another based on the therapeutic exercise that exerts its effect through more neurophysiological mechanisms. By observing the effects of these two therapies, we will try to analyze and gain a better understanding of the mechanisms that cause postural instability in patients with this type of pain. Our results intend to present whether the provocative mechanisms have a more structural component, or instead are caused by alterations produced at the level of the central nervous system by its sustained exposure to pain. In addition, we intend to establish relationships between clinical improvement in relation to pain with improvement in postural stability of the subjects and to analyze the differences depending on the treatment applied.

We have designed a randomized, controlled, double-blinded clinical trial, with the aim that our study can contribute to increase scientific knowledge on this matter and initiate new lines of future research.

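### The double-blind label does not fit the exercise arm: participants can be masked at most between manual therapy and sham

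*Protocol article*

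**What the plan says.** The claim appears in three places in the protocol article, each time without qualification.

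- Trial design: "This study is a randomized, controlled, parallel, double-blind, three-arm clinical trial of treatment".
- Blinding: "The evaluator and participants in the study will be blinded during the entire process".
- Discussion: "We have designed a randomized, controlled, double-blinded clinical trial".

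The Interventions section describes the three arms as follows.

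- **Manual therapy:** a thoracic manipulation, cervical mobilization and suboccipital inhibition. "This protocol will be applied in the three treatment sessions, one per week".
- **Therapeutic exercise:** a programme that "will be taught to patients in the first session and should be done once a day during the 3 weeks of treatment". It grows from two exercises in week 1 to four in week 2 and six in week 3.
- **Sham:** hands are laid on the neck for 3 min while "the physiotherapist will simulate the technique of suboccipital inhibition". Contact with a switched-off laser pointer follows for 10 s.

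No sham exercise or double-dummy arrangement is described.

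**The concern.** A person who has been taught a set of exercises and does them every day knows that exercise is the treatment received. A person who receives only manual contact knows that it is not exercise. The statement that participants are blinded throughout is therefore contradicted by the article's own description of the arms. This is not a detail left to a fuller document, because no further text could make participants unaware of what they do daily.

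Blinding of participants matters most where the participant supplies the measurement. If expectation differs between a self-performed programme and passive treatment, it can shift reported pain and disability, and a blinded evaluator gives no protection against that. The Hypothesis section claims a benefit over sham on pain as well as on postural stability, and links improvement in one to improvement in the other. The Discussion intends to infer structural or central mechanisms from how the two therapies differ. A reader who takes the double-blind label at face value would credit these comparisons with a protection they lack.

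**Working it through.** No arithmetic beyond counting applies, and there is no figure in the plan to reproduce. The check sets the arm and outcome descriptions side by side.

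**Step 1: which contrasts can be masked to the participant.** Three arms give three pairwise contrasts.

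| Contrast | What the participant experiences | Masking possible? |
|---|---|---|
| Exercise vs sham | daily taught exercises vs hand placement and an inactive laser | No |
| Exercise vs manual therapy | daily taught exercises vs hands-on techniques | No |
| Manual therapy vs sham | three hands-on techniques vs imitation of one | At most, and in part |

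Two of the three contrasts cannot be masked.

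**Step 2: how close the sham is to manual therapy.** The timed manual therapy components are mobilization, 3 × 2 min = 6 min, and suboccipital inhibition, 3 min. Together that is 9 min, plus an untimed manipulation. The sham is 3 min of hand placement plus 10 s of laser contact. It imitates suboccipital inhibition only and adds an element that manual therapy lacks. A participant who does not know what the other arm receives could still take it for active treatment, so masking is possible here but not assured.

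**Step 3: how far each outcome depends on the participant** (Outcome measures section).

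| Outcome | How the value arises | Exposure |
|---|---|---|
| NDI | self-assessment questionnaire | High |
| VAS | participant marks a line | High |
| PPT | algometer reading by the evaluator, mean of three, stopped at the participant's spoken signal | Intermediate |
| OBI | index from a stabilometric platform | Lower, though it reflects the participant's performance |

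Three of the four outcomes depend on the participant's response, but not equally.

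**Step 4: where the exposed outcomes enter.** The Primary objective section concerns postural stability only, and the Sample size calculation rests on OBI. Pain and disability form the Secondary objective, although the Abstract lists them within the primary aim. The Statistical analysis section correlates pain improvement with postural stability, so any expectation effect on reported pain also enters that association.

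**Step 5: the evaluator.** Nothing in the article contradicts evaluator blinding. It can be kept up, provided that participants do not reveal their arm at the evaluations in weeks 2, 4 and 12.

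**The case against.** The strongest reply is that an exercise arm can never be masked, that the primary outcome is instrument-measured, and that a change of label removes no bias. Much of this stands. The design is not at fault for including exercise. OBI is the less exposed measure, and allocation, measurements and planned tests are untouched. This limits the severity. It does not rescue the claim, which asserts a property that the design lacks.

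It could also be said that participants may not be told of the other arms or of the hypothesis, so that all three groups believe they are being treated. The article does not say, and as consent material is not part of what was reviewed, its silence cannot be held against the plan. Such an arrangement could reduce differences in expectation. It would still not be blinding to the treatment received.

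A reader might infer more than the document supports in four ways:

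- **That everyone who receives hands-on contact knows the allocation.** Such participants know that they are not exercising, but sham participants need not know that they are in the sham arm.
- **That the primary objective is compromised in the same way as pain.** The Primary objective section ties it to postural stability, measured by platform.
- **That expectation effects swamp the treatment effect or make it uninterpretable.** The document gives no basis for their size.
- **That evaluator blinding fails too.** No text suggests this.

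**Conclusion.** The unqualified claim of participant blinding is wrong as written and should be corrected. It fails for two of three pairwise contrasts and is only partly attainable for the third. The consequence falls mainly on VAS and NDI, less on PPT, and on the association between pain and postural stability. OBI is less exposed but not immune.

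The conclusion assumes only that participants recognise whether they have been taught and are performing exercises. Neither the direction nor the size of any bias can be derived from the document. The correction does change what the pain and disability comparisons with exercise can support. Because the outcome behind the primary objective and the sample size is instrument-measured, this is a point that should be fixed, not one that undermines the trial.

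**What to change.** 1. Replace double-blind with assessor-blinded in the Trial design section and the Discussion, and reword the Blinding section to match.
2. Limit any statement on participant masking to manual therapy versus sham, and note that the sham imitates one of the three techniques.
3. State that the exercise contrasts on VAS, NDI and PPT, and the association between pain and postural stability, will be interpreted as not participant-blinded.
4. Rest the main conclusion on OBI, consistent with the Primary objective and Sample size calculation sections.
5. Ask participants not to disclose their treatment to the evaluator, which protects the blinding that can be achieved.

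The cost is a less favourable blinding label, some rewording and one instruction to participants. No extra staff, procedures or participants are needed.

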### Statistical analysis

The statistical analysis will be carried out using IBM-SPSS Statistics 24 software. The normality test applied to all the variables will be the Kolmogorov-Smirnov test. For the contrast of intragroup hypotheses, Student’s *t* test for paired variables will be applied in the case of parametric distributions and Kruskal-Wallis *H* for non-parametric distributions. For the intergroup hypothesis contrast, one-factor analysis of variance (ANOVA) will be used in the case of parametric distributions and Kruskal-Wallis *H* for non-parametric distributions. Post hoc analysis will be obtained through Bonferroni’s contrast for parametric distributions and Mann-Whitney’s *U* for non-parametric ones. Associations between pain (clinical improvement) and PS will be analyzed through Pearson’s *R* or Spearman’s rho. The confidence level used will be 95% (0.05), and the power of the study will be 90% (0.1).

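### The Kolmogorov-Smirnov check that chooses between parametric and rank tests is insensitive at about 20 per arm and is not tied to paired differences or residuals; minor, but worth correcting together with the paired rank test

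*Protocol article*

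**What the plan says.** The Statistical analysis section sets one gatekeeper: "The normality test applied to all the variables will be the Kolmogorov-Smirnov test". Three choices follow from it.

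- Within groups, Student's t "test for paired variables will be applied in the case of parametric distributions and Kruskal-Wallis *H* for non-parametric distributions".
- Between groups, "one-factor analysis of variance (ANOVA) will be used in the case of parametric distributions and Kruskal-Wallis *H* for non-parametric distributions".
- Post hoc, "Post hoc analysis will be obtained through Bonferroni’s contrast for parametric distributions and Mann-Whitney’s *U* for non-parametric ones".

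The section does not say whether a variable means a score, a change or a residual, whether the test is run per arm or on all arms together, or whether the limit allows for an estimated mean and SD (the Lilliefors correction).

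The Sample size calculation section enrols 66 patients, "each group with at least 20 subjects". Its planning values are "a unilateral contrast, a typical deviation of 10% (0.10), a minimum difference to detect of 9.8% (0.098"). The protocol gives no distribution for the Overall Balance Index (OBI), VAS, PPT or NDI.

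**The concern.** There are two weaknesses.

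**The quantity.** A paired t test relies on the within-person differences being near normal, and ANOVA on the residuals within arms. Skewed scores can have normal differences, and the reverse. A check on the scores can therefore send the analysis down the wrong branch.

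**The sensitivity.** Kolmogorov-Smirnov is a weak detector of skew in samples of about 20, and weaker still if its limit treats the mean and SD as known.

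Skew is plausible here: OBI is built from deviations, and VAS and NDI cannot fall below zero. Under skew, a rank test can be more powerful than ANOVA between groups. What is at stake is power, and whether the plan's switch does what it is there to do.

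**Working it through.** **1. Inputs.** From the Sample size calculation section: 66/3 = 22 per arm, with a floor of 20; after the stated 15% loss, 22 × 0.85 = 18.7. The design shift is 0.098/0.10 = 0.98 SD. The plan's own figure of 10 per group reproduces if three means lie 0.098 apart: noncentral F with alpha 5% and power 90% gives 8 per group, and 8/0.85 = 9.4, rounded up to 10. That figure plays no further part; 20 per arm is used below. The shape of the outcomes is an assumption: gamma(4) (skew 1), lognormal with sigma 0.4, 0.5 and 0.8 (skew 1.3, 1.75, 3.7), and exponential (skew 2).

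**2. Detection of skew in one arm of 20.** The statistic is D = max |F_n(x) − Φ((x − mean)/SD)|, compared with the Lilliefors limit or the uncorrected limit. There were 4,000 samples per cell (3,000 for Shapiro-Wilk).

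| Skew | K-S, Lilliefors | K-S, uncorrected | Shapiro-Wilk |
|---|---|---|---|
| 1 | 18% | 0.2% | 28% |
| 1.3 | 25% | 0.4% | 38% |
| 1.75 | 34% | 1% | 52% |
| 2 | 59% | 4% | 84% |
| 3.7 | 64% | 10% | 84% |

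**3. Between-group power of the whole rule.** Each run uses Kruskal-Wallis if the check rejects and ANOVA otherwise. One arm is shifted, with 6,000 trials per row. Per-arm versions switch if any arm is flagged. Entries are percentages.

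| Shift, skew | ANOVA always | Per-arm Lilliefors | Pooled Lilliefors | Per-arm uncorrected | Pooled uncorrected | Shapiro-Wilk |
|---|---|---|---|---|---|---|
| 0.98 SD, normal | 88.7 | 88.4 | 88.5 | 88.7 | 88.7 | 88.5 |
| 0.98 SD, 1 | 89.2 | 91.8 | 90.4 | 89.4 | 89.3 | 92.6 |
| 0.98 SD, 1.75 | 88.5 | 96.5 | 94.7 | 89.7 | 89.4 | 97.4 |
| 0.98 SD, 3.7 | 88.7 | 99.6 | 98.9 | 94.3 | 94.1 | 99.7 |
| 0.6 SD, normal | 47.5 | 47.1 | 47.2 | 47.5 | 47.5 | 47.5 |
| 0.6 SD, 1.75 | 49.8 | 63.8 | 62.5 | 51.5 | 52.3 | 65.8 |
| 0.6 SD, 2 | 49.4 | 76.1 | 75.4 | 54.2 | 59.2 | 76.9 |

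Gain from Shapiro-Wilk over each reading of the plan:

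- Per-arm Lilliefors: at most 65.8 − 63.8 = 2.0 points. Three arms give three chances to flag, so some arm is flagged in 46% to 96% of skewed trials.
- Pooled Lilliefors: at most 4.3 points (83.3 − 79.0, at 0.8 SD and skew 1.3).
- Uncorrected, 0.98 SD: about 3 to 8 points.
- Uncorrected, 0.6 SD, skew 2: 76.9 − 59.2 = 17.7 points pooled, and 76.9 − 54.2 = 22.7 per arm.

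A further set of runs with lognormal sigma 0.3 to 0.7 and shifts of 0.6 to 0.98 SD gave 0-2, 1-5 and 2-17 points against per-arm Lilliefors, pooled Lilliefors and uncorrected K-S.

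**4. Type I error.** With no shift, every version of the between-group switch rejected in 4.2% to 5.8% of trials.

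**5. Does the quantity matter between groups?** Hardly. With normal data and one arm shifted by 0.98 SD, Lilliefors rejected 4.6% of pooled scores and 4.8% of residuals.

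**6. Does it matter within groups?** Yes, in both directions.

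*Skewed scores, normal differences.* With an assumed pre-post correlation of 0.5 to 0.9, Lilliefors on the baseline score rejects 11% to 33% of the time, against 5% on the differences. If pre and post scores are both tested (lognormal sigma 0.5-0.8), 41-65% of samples are flagged. In an assumed example, the score check gave power of 52-61% and the difference check 82%. Most of that loss arises because flagged data go to Kruskal-Wallis, which ignores pairing.

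*Skewed differences.* Take 20 pairs, baseline SD 1, and lognormal differences with SD 0.7 and mean 0.49. For sigma 0.3/0.5/0.7 the paired t test has 90/95/98% power, Wilcoxon signed-rank 85/90/97%, and Kruskal-Wallis 8-10%. Shapiro-Wilk on the differences, with Kruskal-Wallis kept as the alternative, yields 70/51/32%. The middle value checks by hand: Shapiro-Wilk flags 51.7%, so 0.483 × 95 + 0.517 × 9 = 50.5%.

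**The case against.** The strongest reply is that the text does not commit the sponsor to the bad version. It says variables, not raw scores, and a change score is also a variable. It says neither pooled nor uncorrected. Tested within each arm, a score minus its arm mean is already the residual, so the between-group check may look at the right quantity. This is a condensed article, and how a normality check is run can be left to an analysis plan. All of that stands, and it is why the between-group size must be given as a range.

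A reader might infer that the plan will in fact pick the weaker test and lose power. The documents do not support that. They give no skew and no choice of limit, and with per-arm Lilliefors the difference is 2 points or less. Nor does missed skew pull the trial materially below its power under normality: at 0.98 SD ANOVA keeps 88.4% to 89.2% under every shape, against 88.7% for normal data. What is forgone is a possible gain from ranks. A reader might also infer invalid results; the type I error of the between-group switch gives no sign of that.

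Two further objections hold. Changing the normality test alone would do harm in the paired analysis, as step 6 shows. And any data-driven switch is weaker than one analysis fixed in advance. Neither removes the point: the named test is insensitive at this sample size, and nothing ties it to the differences on which the paired t test depends.

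**Conclusion.** The concern holds in a limited form, and its severity is minor. The plan lets a test that is insensitive at about 20 per arm decide every analysis branch, without directing it at paired differences or residuals.

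Between groups the cost is conditional on skew: about 0 to 5 points of power with the Lilliefors correction, and more without it (up to about 17 points for pooled scores, and 23 for per-arm testing under strong skew and a 0.6 SD shift). Within groups a valid paired t test can be displaced, at a larger cost in the assumed example, and the unpaired alternative accounts for most of that cost.

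The sizes rest on assumed shapes, 20 per arm, and pure shifts with the same shape in each arm. The type I error result covers the overall between-group test under those conditions, not the post hoc comparisons.

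**What to change.** Make two changes to the Statistical analysis section, in the same edit.

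1. Replace the normality sentence with: *Normality will be assessed with the Shapiro-Wilk test and Q-Q plots, on the within-person differences for intragroup tests and on the within-arm residuals for between-group tests.*
2. Name the Wilcoxon signed-rank test, in place of Kruskal-Wallis, as the intragroup non-parametric test. The first change should not be made without this one.

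The clause on post hoc tests gives no adjustment for Mann-Whitney. That is a separate matter, but it should be settled at the same time, since the rank branch will be used more often.

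The cost is two short edits, with no extra patients or data. In the simulated between-group tests there was no material loss under normality. The downside is that rank tests will be used somewhat more often, with effects then reported as shifts or medians. A sounder but larger rewrite would fix one analysis per outcome in advance, with residual checks and a rank-based sensitivity analysis, and drop the switch.
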